## Abstract

**Background:**

To date, surgeons and physicians have found positive results treating metabolic syndrome with surgical and non-surgical weight loss therapies. The purpose of this study was to evaluate changes in telomere length in patients with metabolic syndrome after weight loss.

**Methods/design:**

This study is a three-arm randomized controlled trial. The first group is composed of patients who have undergone stapleless bypass surgery (one anastomosis gastric bypass with an obstructive stapleless pouch and anastomosis (LOAGB-OSPAN)). The second group of patients underwent standard gastric bypass surgery (laparoscopic mini-gastric bypass-one anastomosis gastric bypass (LMGB-OAGB). The patients in the third group received non-surgical weight loss therapy, including a hypocaloric diet with energy restriction (− 500 kcal/day).

The aim is to compare changes—telomere length, body mass index, comorbidities, and quality of life—in patients with metabolic syndrome after weight loss.

**Discussion:**

To the best of our knowledge, this is the first randomized study to simultaneously compare the effects of surgical and non-surgical weight loss on changes in telomere length. It could provide a solution to the growing problem of metabolic syndrome. Normalization of the body mass index results in improvements in the health of patients with metabolic syndrome.

**Trial registration:**

ClinicalTrials.gov, NCT03667469. Registered on 11 September 2018.

**Electronic supplementary material:**

The online version of this article (10.1186/s13063-019-3304-9) contains supplementary material, which is available to authorized users.

## Background

The prevalence of obesity in the general population in Kazakhstan in 2017 was greater than 20%. The increase of the prevalence of obesity over the past 5 years was 3.9% [1]. Metabolic syndrome (MetS), which is the result of abdominal obesity, is a complex combination of symptoms that are risk factors for cardiovascular disease and manifestations of type 2 diabetes or prediabetes, non-alcoholic fatty liver disease, and dyslipidemia. Clinical MetS plays a leading role in reducing the life expectancy and increasing the mortality of Kazakhstan’s population [2].

Metabolic surgery should be recommended to treat type 2 diabetes in patients with class III obesity (BMI ≥ 40 kg/m2) and in those with class II obesity (BMI 35.0–39.9 kg/m^2^) when hyperglycemia is inadequately controlled by lifestyle and optimal medical therapy. Surgery should also be considered for patients with type 2 diabetes and BMI 30.0–34.9 kg/m^2^ if hyperglycemia is inadequately controlled despite optimal treatment with either oral or injectable medications. These BMI thresholds should be reduced by 2.5 kg/m^2^ for Asian patients [3].

Non-surgical weight loss therapies with an energy deficit of 500–1000 kcal/day should produce an approximately 10% body weight reduction over 6 months [4]. Reducing excess body weight positively affects the clinical course and life expectancy of patients with MetS [5]. Currently, surgeons and physicians have found positive results treating patients with MetS via surgical and non-surgical weight loss therapies [6]. The use of endoscopic staplers for surgical weight loss does not exclude the emergence of serious surgical complications, such as bleeding and leakage along the stapled suture line [7]. Therefore, the advantages of using a band in gastric bypass surgery justify its use from a safety point of view [8, 9].

It is known that increased systemic inflammation and oxidative stress associated with obesity can accelerate ageing, and telomere length (TL) can serve as an indicator of ageing at the cellular level [10]. Obesity has a known association with a shorter TL [11]. Weight loss in obese men is associated with increased telomere length [12]. However, the association of a reduction in body weight with a change in life expectancy remains unclear.

## Methods/design

### Study aim

The aim of this study was to evaluate the changes in telomere length in patients with MetS after weight loss induced by stapleless laparoscopic anastomosis gastric bypass–obstructive stapleless pouch and anastomosis (LOAGB-OSPAN), laparoscopic mini-gastric bypass–one anastomosis gastric bypass (LMGB-OAGB), and non-surgical weight loss therapy with energy restriction (− 500 kcal/day).

### Organization

The principal investigator (PI) is responsible for the overall project and for organizing steering committee meetings. An independent steering committee will be responsible for ensuring the overall safety of participants, coordinating study meetings, supervising the study, monitoring data safety, and overseeing the quality control.

Patient follow-up for all groups (1–3) will be carried out by the surgeon and endocrinologist and nutritionist.

### Study design

The study is designed as an interventional, prospective, randomized, controlled, single-center clinical trial. Patient enrolment started on May 24, 2018, and the last patient is expected to be included in the study on November 4, 2019. The study we be completed on September 30, 2020.

The ethics committee of the Corporate Fund “University Medical Centre” (UMC) has granted ethics approval for this study (May 24, 2018, approval number 5).

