### Eligibility criteria

The inclusion criteria are as follows:Aged from 18 to 55 years.BMI from 30 to 50 kg/m^2^.Metabolic syndrome (MetS) with abdominal adiposity according to the presence of at least two of the following components of MetS: increased fasting plasma glucose levels detected before diabetes to pre-diabetes (HbA1 = 5.7–6.4 or a threefold increase in fasting plasma glucose > 5.6 mmol/l); previously diagnosed type 2 diabetes (HbA1 > 6.5 or glucose > 6.1); arterial hypertension (AD 130/85 mmHg or receiving antihypertensive therapy); increased triglyceride levels (> 1.7 mmol/L or receiving specific treatment for this disorder); decreased levels of high-density lipoprotein cholesterol (HDL-C < 1.03 mmol/L in men and < 1.29 mmol/L in women or receiving treatment for this disorder). The patient population will be included in the study if inadequately controlled despite optimal treatment for their diabetes, hypertension, and lipid disorders.Available to receive treatment for 6 months, with the possibility of follow-up.Provided written informed consent for randomization and treatment.

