### General procedures and monitoring

#### Data collection and management

Treatment-related data are collected at V1 (before intervention) and at V2 (the start of the intervention or the baseline). According to the study protocol, follow-up data will be collected from V1 to months 6 (V3) and 12 (V4). Data collection begins on the day a participant signs the informed consent and continues until the termination of the trial or until the participant withdraws from the trial for any reason. If participants discontinue or deviate from the study protocols, the investigators will attempt to minimize the missing data. All original data are kept in chronological order for verification. Original data are transferred in a timely manner to a paper-based case report form (CRF) and an electronic database system located in a guarded facility at the trial site. Access to the study data is restricted. The PI will have access to the final dataset. An independent steering committee will monitor and examine adherence to the study protocol (Figs. 1 and 2).

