### Outcome measures

#### Primary outcome measurement

Changes in the length of leukocyte telomeres

Changes in leukocyte TL will be determined in the patients in the three groups 6 and 12 months after surgery.

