## Trial status

At the time of the initial manuscript submission, recruitment had started (May 24, 2018), but it has not been completed. The last patient is expected to be included in the study on November 4, 2019.

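### The planned completion date falls 35 days before the last patient's 12-month visit, so some patients cannot supply the 12-month primary measurement within the study

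*Protocol article*

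**What the plan says.** All references are to the protocol article.

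- **Calendar.** Study design opens enrolment on a fixed date ("Patient enrolment started on May 24, 2018") and then states that "the last patient is expected to be included in the study on November 4, 2019. The study we be completed on September 30, 2020". Trial status repeats the recruitment date: "The last patient is expected to be included in the study on November 4, 2019".
- **Primary outcome.** Under Primary outcome measurement: "Changes in leukocyte TL will be determined in the patients in the three groups 6 and 12 months after surgery".
- **Visits.** Data collection and management says "follow-up data will be collected from V1 to months 6 (V3) and 12 (V4"). The same section makes V1 the pre-intervention visit and V2 the start of intervention, or baseline. It ends data collection when the trial terminates or the participant withdraws.
- **Entry.** One inclusion criterion reads "Available to receive treatment for 6 months, with the possibility of follow-up".
- **Off-schedule and missing data.** The section on populations and missing data keeps examinations done outside their planned time in the analysis. It also provides for multiple imputation, mixed models and weighted estimating equations.

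**The concern.** The article prints the last-inclusion date, the completion date and the month of the final visit, and the three do not fit together. The last patient cannot reach month 12 before the study closes, and the article makes no provision for a V4 after closure or for late entrants to skip it.

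Month 12 is a stated time point of the primary outcome. It is also a time point for the secondary outcomes of BMI, comorbidities and quality of life. The resulting gaps would come from the calendar alone, would fall on the latest entrants, and could not be recovered once the study had closed. With 20 patients per arm, a planned loss of primary data is better removed than imputed.

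**Working it through.** **Inputs**

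| Quantity | Value | Section |
|---|---|---|
| Enrolment opens | 24 May 2018 | Study design |
| Last inclusion (expected) | 4 November 2019 | Study design; Trial status |
| Study completed | 30 September 2020 | Study design |
| Primary time points | months 6 and 12 | Primary outcome measurement |
| Final visit V4 | month 12 | Data collection and management |
| Screening before treatment | 0 to 7 days | Study population/participants and recruitment |
| Patients | 60 (20 per arm) | Randomization; Sample size |

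**1. Can the completion date be reproduced?** Three constructions were tried:
- last inclusion + 6 months = 4 May 2020
- last inclusion + 12 months = 4 November 2020
- last inclusion + 7 days + 12 months = 11 November 2020

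None gives 30 September 2020.

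**2. Follow-up available to the last patient.** From 4 November 2019 to 30 September 2020 is 331 days; 331 / 30.4375 = 10.9 months.

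**3. Shortfall.** From 30 September 2020 to 4 November 2020 is 35 days. If treatment starts 7 days after inclusion and month 12 is counted from treatment, it is 35 + 7 = 42 days. If instead the inclusion date is the treatment date and month 12 is counted from a V1 held 7 days earlier, it is 35 − 7 = 28 days. The conflict remains under every origin that the article allows.

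**4. Who is affected.** Month 12 falls by 30 September 2020 only for patients included by 30 September 2019. Enrolment runs 529 days (24 May 2018 to 4 November 2019), and the last 35 of those days are too late: 35 / 529 = 6.6%.

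**5. How many.** The article gives no accrual pattern. Assuming uniform accrual:
- counted from inclusion: 60 × 35 / 529 = 3.97, about 4 patients
- with the 7-day lag: 60 × 42 / 529 = 4.76, about 5 patients

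Whatever the pattern, at least the last patient is affected if the dates are kept. Late-loaded accrual would raise the number.

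**6. Month 6.** The last patient's 6-month visit is due on 4 May 2020, 149 days before completion, so that measurement is safe.

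**7. Cost in precision.** With 56 instead of 60 patients at month 12, the standard error rises by a factor of √(60/56) = 1.035, about 3.5%.

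**The case against.** The strongest defence is that the effect is small and the analysis plan can absorb it. The 6-month measurement is complete for everyone, the loss at month 12 is about 4 patients under an assumed accrual pattern, and the standard error rises by only about 3.5%. Loss driven by the calendar in randomised arms is not obviously biasing. An early last visit would stay in the analysis, and imputation or mixed models are planned. The last-inclusion date is only expected, and the full protocol may hold a visit window.

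Most of this is fair as to size, but it does not resolve the conflict. A sample at 10.9 months is not the 12-month outcome that the article defines. A window would have to reach at least 35 days early to cover the last patient, and the article states none. Recruitment might close sooner, but the plan as printed says otherwise in two places.

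A reader might also infer more than the text supports:

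- **That entry demands only 6 months' availability, so patients unable to attend month 12 are admitted.** The criterion attaches 6 months to treatment and adds follow-up as a further element. Its length is unstated; it is not absent.
- **That Group 3 has no time origin.** The outcome wording does refer to surgery for all three groups, and Group 3 has none. But V2 is defined as the start of intervention, which serves every arm, and the mention of V1 can be read as the span of data collection. This is loose wording.
- **That the surgical arms lose more.** Screening is 0 to 7 days before treatment, with no distinction by arm. Even if a full 7-day lag fell on the 40 surgical patients alone, it would add 40 × 7 / 529 = 0.5 patient under uniform accrual. An imbalance is speculation.

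**Conclusion.** The point holds as a conflict of dates. Counted from inclusion, the study ends 35 days before the last patient's month 12, and patients included after 30 September 2019 cannot reach V4 within it. This follows from the printed dates without any assumption. The count of about 4 in 60 rests on uniform accrual, which is assumed; the certain minimum under the printed plan is one patient. Only the month-12 measurements are affected, and the main consequence is a modest, avoidable loss of precision at a primary time point. The documents do not show bias between arms, loss of the whole primary outcome, or an eligibility rule that itself causes the loss. The case for correction is that the loss is certain under the printed plan, irrecoverable after closure and cheap to prevent.

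**What to change.** Reconcile Study design and Trial status with the month-12 visit in one of two ways:

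- Move completion to no earlier than 4 November 2020, or 11 November 2020 if treatment may start up to 7 days after inclusion, and add any late visit window that the full protocol specifies.
- Keep 30 September 2020 and close inclusion by 30 September 2019, or by 23 September 2019 (30 − 7) if the same 7-day lag is allowed for.

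Two minor clarifications should accompany it. Under Primary outcome measurement, replace the reference to surgery with one origin that applies to all three arms, such as V2 (start of intervention) or randomisation. Under Eligibility criteria, state that the required availability for follow-up extends to month 12.

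The first route costs 35 to 42 days, about five to six more weeks of follow-up, and a date amendment, with no extra patients. The second costs the last 35 (or 42) days of recruitment, so it suits only if 60 patients can be enrolled by then.

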### Study population/participants and recruitment

Recruitment will be carried out by responsible bariatric surgeons with a minimum of 10 years of bariatric surgery experience in the Department of Surgery, National Scientific Center for Oncology and Transplantation (Astana, Kazakhstan). Screening will be performed on day − 7–0 prior to treatment to ensure that the patients fulfil the inclusion criteria. Patients will attend an informational meeting, at which they will be informed about the study purpose, process, and risk and benefits. Patients fulfilling the study criteria who sign the informed consent form will start treatment in accordance with the standard procedures of the trial site. Informed consent will be obtained from each participant by the investigators. During the trial, the investigators will continue to provide additional health care or compensation for participants’ health care needs that arise as a direct consequence of their participation in the trial.

### Eligibility criteria

The inclusion criteria are as follows:Aged from 18 to 55 years.BMI from 30 to 50 kg/m^2^.Metabolic syndrome (MetS) with abdominal adiposity according to the presence of at least two of the following components of MetS: increased fasting plasma glucose levels detected before diabetes to pre-diabetes (HbA1 = 5.7–6.4 or a threefold increase in fasting plasma glucose > 5.6 mmol/l); previously diagnosed type 2 diabetes (HbA1 > 6.5 or glucose > 6.1); arterial hypertension (AD 130/85 mmHg or receiving antihypertensive therapy); increased triglyceride levels (> 1.7 mmol/L or receiving specific treatment for this disorder); decreased levels of high-density lipoprotein cholesterol (HDL-C < 1.03 mmol/L in men and < 1.29 mmol/L in women or receiving treatment for this disorder). The patient population will be included in the study if inadequately controlled despite optimal treatment for their diabetes, hypertension, and lipid disorders.Available to receive treatment for 6 months, with the possibility of follow-up.Provided written informed consent for randomization and treatment.

### Exclusion criteria

The exclusion criteria are as follows:Aged less than 18 years or more than 55 yearsBMI less than 30 kg/m^2^ or more than 50 kg/m^2^Drug addiction or alcohol consumptionComplete immobilization of the patient (paresis/paralysis)Presence in the anamnesis of a history of bariatric surgeryInsulin-dependent diabetesMental disorders or the use of antidepressantsSocially vulnerable categories (according to ethical principles)Patients who do not understand the purpose of the studyLack of informed written consent

### Withdrawal criteria

If adverse events, especially severe adverse events, occur, researchers may consider withdrawal of patient(s) based on ethical and safety concerns.Patients drop out of the study.Patients voluntarily withdraw their informed consent.Serious violation of the study protocol by the subjects or investigators.Other reasons that the researchers believe are acceptable reasons for quitting the study.

### Randomization

Informed consent will be obtained from each participant before patient enrolment in the study. Patients who meet all the inclusion criteria and none of the exclusion criteria will be consecutively included and randomized into one of the three study arms by the study statistician, who is not involved in the enrolment, assignment, or assessment of patients, according to a random allocation sequence generated by Stata 7.0. The randomization list is kept strictly confidential. Allocation concealment is ensured with the use of sequentially numbered, identical, opaque, sealed envelopes (*n* = 60). The intervention will be communicated to the patient by a nurse who has no involvement in the enrolment or assessment of patients and who will open the sealed envelope during the visit before surgery.*Group 1 (A)*. The patients in Group 1 (*n* = 20) are treated by laparoscopic one anastomosis gastric bypass with an obstructive stapleless pouch and anastomosis (LOAGB-OSPAN).*Group 2 (B).* The patients in Group 2 (*n* = 20) are treated by laparoscopic mini-gastric bypass-one anastomosis gastric bypass (LMGB-OAGB) according to standard surgical procedures.*Group 3 (C).* The patients in Group 3 (*n* = 20) are treated by hypocaloric diet therapy with energy restriction. Standard diet for men and women of 1500 kcal/day − 500 kcal/day = 1000 kcal/day (an energy deficit of 500–1000 kcal/day).

### Blinding

In this study, the single-party independent evaluation method is used to evaluate the outcomes of the study. The outcome analyzer, study statistician, patients, and surgeons are blinded.

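### The Blinding section lists patients and surgeons as blinded, but the protocol's own procedures tell both the arm, so quality of life is an unblinded outcome

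*Protocol article*

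**What the plan says.** The Blinding section has two sentences. The first describes how outcomes are assessed: "the single-party independent evaluation method is used to evaluate the outcomes of the study". The second lists who is blinded: "The outcome analyzer, study statistician, patients, and surgeons are blinded".

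The Randomization section describes how the allocation reaches the patient: "The intervention will be communicated to the patient by a nurse who has no involvement in the enrolment or assessment of patients". The same nurse "will open the sealed envelope during the visit before surgery". Groups 1 and 2 receive two different laparoscopic bypass operations. Patients in Group 3 "are treated by hypocaloric diet therapy with energy restriction". The three groups are labelled A, B and C beside the treatment each one receives.

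The same section says patients are "randomized into one of the three study arms by the study statistician, who is not involved in the enrolment, assignment, or assessment of patients". It calls the list confidential but does not say who holds it.

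Under Organization: "Patient follow-up for all groups (1–3) will be carried out by the surgeon and endocrinologist and nutritionist".

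**The concern.** A statement of who is blinded is what a reader uses to judge how far each result could be coloured by knowledge of treatment. Here the statement covers the two parties whose knowledge of the arm is hardest to avoid when surgery is compared with diet.

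What is at stake is the reading of the softer outcomes. Under Secondary outcome measurements, quality of life is a questionnaire score and comorbidity change is rated by assessing symptoms. Either can shift with the respondent's or assessor's expectations. If the blinding sentence is taken at face value, a difference between surgery and diet on these outcomes looks better protected than it is. The primary outcome, leukocyte telomere length, is a laboratory measure and much less exposed.

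**Working it through.** No arithmetic applies and there is no figure to reproduce. The check sets each of the four parties named in the Blinding section against the procedures stated elsewhere in the article.

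1. **Patients: contradicted.** Randomization says "The intervention will be communicated to the patient by a nurse", and this happens before treatment. Even without that step, a patient assigned to diet knows that no operation took place, and no sham procedure is described.
2. **Surgeons: contradicted.** The operating surgeon has to know which of the two techniques to use. The Discussion distinguishes them as a bypass separated by a band and one separated by a stapler. A patient who is not operated on is in the diet arm. The surgeon also shares in follow-up of all three groups (Organization), so the knowledge is present at the 6- and 12-month visits.
3. **Study statistician: unclear.** Randomization has the statistician randomize patients and, in the same sentence, keeps that person out of assignment. The codes A, B and C are decoded in the text, so an analysis file using them would not be masked. A separate list holder or different codes would allow blinding, but the article mentions neither.
4. **Outcome analyzer: not contradicted.** Nothing in the article gives this person the allocation, and a blinded telomere assay is feasible.

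The count is two parties contradicted, one unclear and one consistent.

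The outcomes follow from this:

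- **Telomere length (primary):** falls to the outcome analyzer, whose blinding stands.
- **Quality of life:** comes from the patients' own responses, and patients know their arm, so it is unblinded.
- **Comorbidity change:** the article does not name the assessor. It is unblinded if the follow-up team judges it, and can be blinded if the outcome analyzer does.
- **Body mass index:** calculated from measured weight and height. The point makes no claim about it.

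**The case against.** The strongest reply is that the Blinding section is loosely worded shorthand. It might mean concealment until the envelope is opened, or masking only between the two operations, with the details left to a full protocol that is not shown. This does not rescue the sentence. Randomization already deals with allocation concealment separately. Masking between the operations is nowhere stated, and it would still be untrue for surgeons and for patients in the diet arm. A fuller document could add detail, but it could not make both statements true.

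Other parts of the reply do stand, and they limit the point:

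- A reader might infer that the statistician cannot be blind. The text conflicts with itself, but it can also be read as the statistician generating a sequence that envelopes and a nurse then carry out. Masked codes at analysis would be compatible with that.
- A reader might see a contradiction between a single-party method and four blinded parties. The phrase describes how outcomes are evaluated. It does not count who is blinded.
- A reader might infer that clinicians who know the arm judge comorbidity, so that two of the three secondary outcomes are unblinded. Organization assigns follow-up to the treating disciplines, not outcome evaluation.
- A reader might infer that the telomere assay is unprotected. It falls under the blinded outcome analyzer, and how samples are labelled is detail an article may leave out.
- No passage says how results will be described, so a misleading report is a risk and not a stated plan.

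**Conclusion.** The blinding statement is wrong as written for patients and surgeons, two of the four parties it names. For the statistician it is unresolved, and for the outcome analyzer it stands. Among the three secondary outcomes, quality of life is unblinded. This assumes only that patients answer the questionnaire themselves, as the reference to individual responses in the missing-data section indicates. Comorbidity change is conditionally at risk, depending on who judges it.

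The document gives no basis for sizing the bias, and none is claimed. Nor does the finding show that the primary outcome is compromised. Open-label treatment with blinded evaluation is a legitimate design. The error is that the article claims a property the trial does not have, and this bears directly on how its quality-of-life comparison between surgery and diet may be interpreted.

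**What to change.** Rewrite the Blinding section to say three things:

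- The trial is open-label for patients and surgeons.
- Outcome evaluation, including the telomere assay, is blinded.
- The analysis uses masked group codes other than the published A, B and C until the primary analysis is locked. The section should say who holds the key, because new codes mask little if the analyst also has the allocation list.

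Reconcile the Randomization sentence on the statistician's role with this text.

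In the conclusions, interpret quality of life as an unblinded, patient-reported outcome. Treat comorbidity change the same way unless the protocol states that the blinded outcome analyzer judges it.

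The cost is one amended paragraph, submitted to the ethics committee as the article already provides for amendments, and a relabelling of groups in the analysis file. Treatment, visits and sample size do not change. The downside is that the trial must be described as open-label.
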